#### Exclusion criteria

Individuals who are pregnant or breast-feedingCurrently receiving prescribed fentanyl in any form, e.g. fentanyl patchPrevious participation in this study (previous receipt of SIFI in an in-hospital clinical setting is not exclusionary)Current use of buprenorphine extended-release (Sublocade®) in any doseUse of buprenorphine-naloxone (Suboxone®) within the previous 3 days

Potential participants will not be excluded based on presence of substances other than fentanyl in the screening UDT, nor on the basis of alcohol use disorder or any other substance use disorder. The intent is to make the protocol applicable in a real-world setting where the majority of individuals who have OUD use multiple other substances in addition to opioids.

## Study treatment

### Induction phase

Once the participant has provided informed consent and is found to be eligible based on results of the screening assessments (Table 1), the participant-readiness threshold will be used to determine the appropriate time to start the induction procedure according to the participant’s level of cravings (Fig. 1)[19].

**Fig. 1 Fig1:**
[figure not shown]
Participant-readiness threshold

When the participant reaches their readiness threshold, fentanyl 400 mcg will be administered intravenously (IV) by a study nurse or physician, with repeat doses every 5 min following assessment of sedation, withdrawal symptoms, and vital signs (Table 1) until the participant indicates comfort or has a Pasero Opioid-induced Sedation Scale (POSS) score of 2 (slightly drowsy, easily roused) [20]. After initial dosing with fentanyl 400 mcg per dose, stepwise increases to 800 mcg, 1000 mcg, and 1200 mcg per dose will be considered once tolerance and safety are established at each dose level. Sedation and vital signs will be reassessed at 5, 10, and 15 min after the final IV fentanyl dose, or until stable.

The total amount of fentanyl administered during the induction phase is the loading dose, to be used in the calculation of the individualized starting dose of methadone or SROM (Figs. 2 and 3)[21, 22].

**Fig. 2 Fig2:**
[figure not shown]
Conversion from Opioid Tolerance to Oral Methadone starting dose for OAT

**Fig. 3 Fig3:**
[figure not shown]
Conversion from Opioid Tolerance to Sustained-release Oral Morphine (SROM) starting dose for OAT

The participant will remain under observation in the clinic while awaiting their first on-study dose of oral OAT.

### Early OAT phase

The specific OAT agent will be chosen prior to study enrolment by the clinic medical team in conjunction with the participant. To determine the first post-induction dose of OAT, the loading dose of fentanyl will be multiplied by 8 and used as a proxy for the participant’s opioid tolerance over 24 h. The multiplier of 8 in this calculation is based in part on anecdotal patterns of unregulated opioid use from the investigators’ experience—approximately 8 times per day. Since the protocol assessment of opioid tolerance reflects a single use, the multiplier of × 8 estimates total daily use. In addition, this approach aligns with the known duration of analgesia and respiratory depression from IV fentanyl boluses, which potentially last 1.5 to 4 h [23]. The calculated opioid tolerance will then be converted to the starting dose for methadone or SROM (Figs. 2 and 3), up to a maximum daily dose of 200 mg or 2000 mg, respectively. From the investigators’ clinical experience utilizing the SIFI protocol in an inpatient setting, participants are generally comfortable for approximately 1–3 h following induction [3], allowing adequate time for calculation, preparation, and dispensing of the individualized starting dose of OAT.

The first on-study oral OAT dose will be administered on the same day as the induction procedure and at least 15 min after the final IV fentanyl dose. On Day 1, participants will receive a maximum total methadone dose of 200 mg or a maximum total SROM dose of 2000 mg, adjusting for any previously prescribed methadone or SROM they received on Day 1 prior to arrival at the clinic. After the post-induction OAT dose is administered, the participant will remain in the clinic for 3 h under observation for ongoing monitoring of safety and vital signs (Table 2), and will receive a cash honorarium for their participation and for the time spent at the clinic. Thereafter, the participant will be offered honoraria for attendance at daily study visits for 7 days for assessment and OAT dispensing (Table 2). If the participant is found to be over sedated (POSS 3 or 4), reports sleeping more than usual, or exhibits any other signs or symptoms of excessive opioid levels, they will be referred to the clinical team for immediate assessment and management, including adjustment of OAT dose if deemed clinically necessary.

**Table 2 Tab2:** Schedule of assessments during early OAT phase (Day 1 through Day 7)

	Before first OAT dose	1 h after first dose	2 h after first dose	3 h after first dose	Day 2	Day 3	Day 4	Day 5	Day 6	Day 7
HR, BP, RR, SpO2	x	x	x	x	x	x	x	x	x	x
POSS	x	x	x	x	x	x	x	x	x	x
COWS	x	x	x	x	x	x	x	x	x	x
Self-reported activity during previous 24 h					x	x	x	x	x	x
ECG	X^a^					X^b^				X^b^
MSQ for OUD meds	X^c^									x
MSQ + 3 questions re: SIFI				x						
Self-reported use of illicit opioids/other substances										x
UDT	X^c^									x
Overdose events req. intervention										x
Hospitalizations/death										x

*OAT* opioid agonist therapy, *UDT* urine drug test, *ECG* electrocardiogram, *POSS* Pasero opioid-induced sedation scale, *COWS* clinical opiate withdrawal scale, *HR* heart rate, *BP* blood pressure, *RR* respiratory rate, *SpO2* oxygen saturation, *MSQ* Medication Satisfaction Questionnaire, *SIFI* symptom-inhibiting fentanyl induction, *OUD* opioid use disorder

^a^For all participants, before start of IV fentanyl induction

^b^Only for participants receiving methadone

^c^At study screening

Methadone recipients who have QT prolongation at their follow-up ECG on Day 3 or Day 7 will be referred to the clinic team for assessment and management. For participants with a stable QTc and without evidence of opioid toxicity, methadone will be maintained at the same dose for the first 7 days.

For participants receiving SROM who meet all the following criteria, SROM doses may be increased by 100 mg every 24 to 48 h as clinically indicated, consistent with current local clinical guidelines [12].Presence of cravings and/or withdrawal symptomsNo evidence of opioid toxicity (e.g. excessive sedation/lethargy, respiratory depression, bradycardia)No evidence of SROM adverse events (e.g. constipation, nausea, vomiting, dyspepsia, abdominal pain, urinary retention, headache, dizziness, hypotension, diaphoresis, xerostomia, dental pain, dysphoria, insomnia) [24]

The magnitude of the SROM dose increase will be based on clinical judgement, taking into account the starting dose and severity of ongoing cravings or withdrawal symptoms.

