### Study population

#### Inclusion criteria

Age 19 years or olderOUD of any severity by DSM-5 Clinical Diagnostic criteria [18]Intentional use of unregulated fentanyl by any route (e.g. injection, inhalation) by participant self-reportUrine drug test (UDT) positive for fentanyl at screening or within 7 days prior to date of screening visit, to confirm the presence of fentanylClinical indication to start OAT with methadone or SROM, or recently started OAT and receiving daily doses of methadone ≤ 150 mg or SROM ≤ 1300 mg (demonstrated to be subtherapeutic for the individual as they are continuing to use unregulated fentanyl)If taking prescribed opioids for safer supply, willing to discontinue them starting on study Day 1 and for at least the first 7 days of the studyWilling and able to provide written informed consent for study participation

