## Discussion

This is the first study to objectively estimate opioid tolerance and use it to determine individualized starting doses of oral OAT for use in an outpatient setting among people who use unregulated fentanyl. This study was initiated in response the inadequacy of current OAT dosing recommendations to address the increasing contamination of the unregulated drug supply with high-potency opioids, mainly fentanyl and its analogues, resulting in an ongoing crisis of opioid overdose and death in BC and elsewhere.

The SIFI procedure involves an IV induction with medical fentanyl, guided by pharmacological principles [33, 34], and has been implemented successfully in an in-hospital setting [3]. To optimize participant safety in this outpatient study, participants will be closely supervised in the clinic during and after the IV fentanyl induction procedure.

A limitation of the SIFI protocol is that sedation observed during the induction procedure may be due to other factors in addition to medically-administered IV fentanyl. In a setting where multi-substance use is common, other contributing factors may include prescription, non-prescription, or unregulated sedating substances (e.g. benzodiazepines, alcohol), and/or catecholamine depletion as a consequence of chronic use of methamphetamine or other stimulants. Operationally, any somnolence or lethargy observed during the induction procedure is attributed to the administered IV fentanyl. If additional sedating factors are present, the consequence would be to underestimate the participant’s opioid tolerance and administer too low a dose of methadone or SROM to fully meet their opioid requirements. This limitation is unavoidable in the interests of participant safety in a setting where the potential effects of concomitant sedating substances cannot be determined or quantified.

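### Methadone or SROM taken on Day 1 before induction counts only toward the Day 1 maximum, so the Day 1 total can exceed need; holding that dose until after induction avoids this

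*Protocol article*

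**What the plan says.** All references are to the protocol article.

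- **Who is eligible.** Recruitment names clients on a suboptimal OAT dose as a source. The Inclusion criteria admit people who recently started OAT, up to 150 mg methadone or 1300 mg SROM daily, a dose "demonstrated to be subtherapeutic for the individual as they are continuing to use unregulated fentanyl".
- **What stops on Day 1.** The Inclusion criteria address safer supply: "If taking prescribed opioids for safer supply, willing to discontinue them starting on study Day 1". The text gives no matching instruction for prescribed methadone or SROM.
- **How the dose is set.** Under Induction phase, "The total amount of fentanyl administered during the induction phase is the loading dose". Under Early OAT phase, "the loading dose of fentanyl will be multiplied by 8 and used as a proxy" for 24-hour tolerance, and the factor of 8 is explained as estimating total daily use. The text has no term for OAT already on board.
- **Same-day OAT.** Early OAT phase caps the Day 1 total at 200 mg methadone or 2000 mg SROM, "adjusting for any previously prescribed methadone or SROM they received on Day 1 prior to arrival at the clinic". The adjustment is attached to the maximum, not to the calculated dose.
- **Acknowledged bias.** The Discussion says other sedating factors, among them "prescription, non-prescription, or unregulated sedating substances", would lead the team to "administer too low a dose of methadone or SROM to fully meet their opioid requirements". It calls this unavoidable because such effects cannot be measured. OAT is not named.

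**The concern.** Titrating to comfort or light sedation measures what is needed on top of what is already acting. A participant's own methadone or SROM taken that morning may be acting fully, partly or not at all when titration starts. If it is not yet acting, the titration finds nearly the whole need and the earlier dose then comes on top.

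Three things are at stake.

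- **Safety.** Any excess falls within Days 1 to 7, the window of the primary safety outcome, and the Background itself warns of methadone accumulation.
- **The dose after Day 1.** Methadone is left unchanged through Day 7 if QTc is stable and there is no toxicity. For these participants the on-study dose and the Day 1 total are different numbers, and the text does not say which one is kept.
- **Interpretation.** Starting dose is a secondary outcome. It would pool estimates of total need with estimates of need above OAT already on board.

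**Working it through.** The plan gives no figure on this point to reproduce, so the check is a dose balance.

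**Inputs from the article:** cap 200 mg methadone or 2000 mg SROM; prior daily dose at most 150 mg or 1300 mg; loading dose times 8 read as total 24-hour need.

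**Assumed, because the documents give no values:**
- N = daily need in mg of the chosen OAT, not above the cap
- P = prescribed dose taken on Day 1 before arrival, with P < N because the current dose must be subtherapeutic
- f = share of P acting at induction
- r = amount still acting from earlier days, as a share of P
- effects add linearly, and the conversion in Figures 2 and 3 is otherwise correct

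**Rule as written (P counts only toward the cap)**

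Calculated dose: C = N − (f + r)P.

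On-study dose: the smaller of C and cap − P, and not below zero.

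Day 1 total: min(cap, N + (1 − f − r)P), and never below P, since P has already been taken.

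The total equals need when f + r = 1. It exceeds need when f + r < 1, by min((1 − f − r)P, cap − N).

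Methadone, N = 100, P = 80, Day 1 total in mg:

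| f | r = 0 | r = 0.25 | r = 0.5 |
|---|---|---|---|
| 0 | 100 + 80 = 180 | 100 + 60 = 160 | 100 + 40 = 140 |
| 0.5 | 100 + 40 = 140 | 100 + 20 = 120 | 100 + 0 = 100 |
| 1 | 100 + 0 = 100 | 100 − 20 = 80 | 80 (C is below zero) |

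SROM, N = 1000, P = 800, f = 0: 1800, 1600 and 1400 mg at r = 0, 0.25 and 0.5.

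Where the cap binds (methadone N = 160, P = 80, f = 0): 240, 220 and 200 mg before the cap, so 200 mg each time, an excess of 40 mg. If N is itself 200 mg, no excess is possible.

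**Days 2 to 7.** For N = 100, P = 80, f = 0, the on-study dose is 100, 80 or 60 mg at r = 0, 0.25 or 0.5, against Day 1 totals of 180, 160 or 140 mg. Keeping the same dose therefore has two possible meanings.

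**If that day's dose is held.** Nothing has been taken that day, so C = N − rP. For N = 100, P = 80 this gives 100, 80 and 60 mg at r = 0, 0.25 and 0.5. The last value is below the 80 mg already judged too low. With a floor at the current dose, the Day 1 total is max(N − rP, P), that is 100, 80 and 80 mg. It cannot exceed N, because r is not negative and P < N. It cannot fall below P. The floor never conflicts with the cap, since P is at most 150 or 1300 mg.

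**The case against.** **Carry-over.** People on daily OAT bring some effect from earlier days, which lowers the loading dose and offsets part of any stacking. This stands. A reader might infer that the rule as written is right only if all of that morning's dose is acting, or that an 80 mg excess is typical. Neither follows: the rule is right whenever f + r = 1, and in the example the excess at f = 0 falls from 80 to 40 mg when r = 0.5.

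**Readiness threshold.** Induction waits for a craving-based threshold, used "to determine the appropriate time to start the induction procedure", so some participants will start when their morning dose is already acting or is offering little relief. How often a dose is recent and not yet acting is unknown.

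**Deduction.** A reader might take the adjustment to mean subtracting P from the calculated dose. The total would then be max(C, P), which never exceeds need, and the error would run toward too little. The wording gives this little support, because the clause qualifies the maximum.

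**Material not shown.** The article condenses a fuller protocol, and Figures 2 and 3 may contain a correction. The missing definition of the adjustment is therefore not itself the point. The point is the stated choice to accept same-day OAT before a tolerance measurement. An instruction to deduct or to cap would not settle the right dose unless it also allowed for what is acting.

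**Safeguards.** The cap, 3 hours of observation, daily sedation and vital-sign checks, dose adjustment and the trial's stopping rules all limit harm. They do so after the dose has been chosen.

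**Underdosing.** The trial exists because low doses drive dropout, so a bare hold is not harmless: it can give less than the participant's current dose. This stands, and it is why the fix includes a floor.

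**Conclusion.** The concern holds in a limited form. As written, a participant whose same-day methadone or SROM has not yet taken effect can receive a Day 1 total above need: 140 to 180 mg against 100 mg in the methadone example at f = 0, depending on carry-over. When f + r is near 1 the total is about right. The Discussion's position that confounding by other substances leads to too low a dose, and cannot be avoided, therefore does not extend to same-day OAT. That dose is known, it can be deferred, and it can push the total up.

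The sizes rest on assumed N, P, f and r and on linear additivity. The documents do not support saying that overdosing is expected or frequent. Participants who took no OAT on Day 1 are not exposed to same-day stacking. No sample size or error rate depends on this. It is an inexpensive improvement to the dosing procedure.

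**What to change.** - Ask participants already on OAT to hold that day's dose until after induction. They are given OAT in the clinic the same day, so the dose is delayed, not lost. Where someone arrives already dosed, move induction to another day if feasible; Table 1 already allows screening and Day 1 to fall on different dates.
- Do not set the post-induction dose below the current prescribed dose. If induction is stopped for suspected overdose, the existing provision for clinic staff discretion should take precedence over this floor.
- The on-study dose and the Day 1 total are then one number, which the Day 2 to 7 methadone rule can use without ambiguity.
- Report starting doses separately by prior OAT status, and name on-board prescribed OAT as a confounder in the Discussion.

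**Cost:** one scheduling instruction, one sentence on the floor, and no new assessments. Some participants will need rescheduling and may not return. Carry-over from earlier days can still leave the dose somewhat low, though not below what the participant was already prescribed.

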## Study design

### Overview of study design

To assess the safety, feasibility, and efficacy of a rapid symptom-inhibiting IV fentanyl induction (SIFI) protocol, we plan to conduct an open-label, single arm, prospective clinical trial with a planned sample size of 50. The primary goal of this pilot study is to identify unforeseen problems with the SIFI procedures that would impact participant safety. If such a problem exists with a prevalence of 5% (i.e. potential to affect 1 out of 20 participants), it will be identified with 92% confidence in a pilot study including 50 participants [15].

Results of this pilot study will be used to inform a subsequent larger and more comprehensive investigation of the SIFI protocol as a treatment strategy for individuals with OUD who intentionally use unregulated fentanyl.

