### Primary outcome

The primary outcome of this study is safety, as defined by occurrence of study drug-related adverse events (including but not limited to sedation, respiratory depression, hypoxia, QT interval prolongation) requiring intervention during the induction and early OAT phases (study days 1 through 7).

The participant’s level of sedation (POSS) and vital signs (heart rate and oxygen saturation by pulse oximetry, blood pressure, and respiratory rate) will be monitored before starting induction, throughout the induction phase, at 5, 10, and 15 min (or until stable) after the final IV fentanyl dose, before the starting dose of OAT is administered, and hourly during the initial 3 h following oral OAT administration. In addition, sedation and vital signs will be assessed once daily for the first 7 days after the initial OAT dose, and during OAT follow-up at 1 month, 3 months, 6 months, and 12 months (Table 3).

In case of suspected opioid overdose (excessive sedation [POSS 3 or 4], respiratory rate below 8 breaths per minute, oxygen saturation below 92% or the participant’s baseline, and/or other signs or symptoms) at any time during the induction or OAT phases or during OAT follow-up, no further IV fentanyl doses will be administered and management will commence immediately according to the clinic overdose response protocol, consistent with established local and provincial guidelines [25].

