Oral methadone can cause prolongation of the QTc (heart rate-corrected QT interval), which in turn is a risk factor for a rare but potentially fatal arrhythmia, Torsades de Pointes (TdP) [26]. An electrocardiogram (ECG) will be performed before commencing the induction and the results will be considered, along with other TdP risk factors, in the clinical decision-making process of selecting methadone or SROM as the appropriate OAT option for that individual [26, 27]. Participants who will receive methadone in this study will be advised during the informed consent process that the risk of arrhythmia is increased with higher doses of methadone. The first 7 days after starting methadone is the time of maximum risk of clinical adverse events, with a peak risk on Day 3 [28]; therefore, an ECG will be repeated on OAT Days 3 and 7 for participants receiving methadone. Any occurrence of QTc prolongation (> 500 ms, or ≥ 60 ms increase from baseline) and/or symptoms consistent with TdP will be managed promptly, consistent with recommendations in national OUD treatment guidelines [27].

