## Monitoring

This pilot study will not have an independent Data and Safety Monitoring Board. Investigators will keep track of adverse events as they occur, and will revise the protocol and informed consent if an excess of adverse events is observed. Specifically, the trial will be put on hold (no new enrollments), revised, and resubmitted to the REB for approval before resuming, in any of the following circumstances:Two serious adverse events that are possibly related to study participation and that occur during the participant’s first week of the study, as serious adverse events are unlikely to be related to the study drugs after methadone or SROM have reached steady-state levels.Study drug-related adverse events requiring intervention (including but not limited to those meeting the criteria for serious adverse events) in 5 or more of the first 10 participants; 10 or more of the first 20 participants; 15 or more of the first 30 participants; or 20 or more of the first 40 participants.

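### Table 2 asks about overdose and hospitalisation/death only on Day 7 although participants are seen daily; asking at each visit is a cheap improvement to the primary safety data

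*Protocol article*

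**What the plan says.** **Schedule (Early OAT phase, Table 2).** Vital signs, POSS, COWS and self-reported activity over the preceding 24 hours are marked on every one of Days 2 to 7. The rows "Overdose events req. intervention" and "Hospitalizations/death" have one mark each, in the Day 7 column.

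**Primary outcome.** It is the occurrence of study drug-related adverse events "requiring intervention during the induction and early OAT phases (study days 1 through 7". The Abstract names opioid toxicity among them. The same section says "The first 7 days after starting methadone is the time of maximum risk of clinical adverse events", and puts the peak on Day 3.

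**Dosing conditions (text below Table 2).** For participants with a stable QTc and "without evidence of opioid toxicity, methadone will be maintained at the same dose for the first 7 days". SROM increases during the week are likewise conditional on there being no such evidence.

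**Monitoring.** There is no independent board. "Investigators will keep track of adverse events as they occur", and enrolment is put on hold after two possibly related serious adverse events in participants' first week, or when drug-related events requiring intervention reach 5 of the first 10, 10 of 20, 15 of 30 or 20 of 40 participants.

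**Other sources.** Secondary outcomes says that overdose, hospitalisation and death during follow-up come from the clinic's electronic medical record (EMR). Table 3 schedules the same two items again at 1, 3, 6 and 12 months. The section on treatment and study discontinuation ends all data collection, EMR included, once a participant withdraws from the study.

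**The concern.** A drug-related overdose that needs intervention on Days 1 to 7 is a primary outcome event. The items marked daily mostly describe the participant at the visit, and the one that looks back is about activity. Someone who was reversed in the community on the evening of Day 3 may look normal on Day 4, and no item marked on Days 4 to 6 asks whether it happened.

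Two things are at stake. The first is timeliness: the hold rule and the dosing conditions both operate before Day 7, but the specific question comes on Day 7. The second is completeness: a participant who stops attending is not there for the Day 7 question, and stopping may well be related to having had an event. In a single-arm pilot of 50 whose purpose is to find safety problems, complete capture of first-week events is what the sample size argument rests on.

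**Working it through.** **1. Timing, read from Table 2.** The column reading can be checked against the text: the ECG row's follow-up marks fall under Day 3 and Day 7, as the Primary outcome section says they should. In the same layout, the overdose and hospitalisation/death rows fall under Day 7 only.

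- Event on Day 3, current schedule: 7 − 3 = 4 days to the first specific scheduled question.
- Same event, question asked at each visit: 4 − 3 = 1 day.
- Gain: up to 3 days. The article gives no enrolment rate, so the number of inductions that could take place in that interval cannot be worked out.

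**2. What each daily item can show about an off-site event that has resolved.**

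| Item marked on Days 2–7 | Period covered | Asks about overdose or admission? |
|---|---|---|
| Vital signs, POSS, COWS | At the visit | No |
| Self-reported activity | Previous 24 h | Not specifically; may prompt disclosure |
| Overdose; hospitalisation/death (Day 7 only) | Not stated; presumably the week | Yes |

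**3. The plan's own figure.** Overview of study design describes an "open-label, single arm, prospective clinical trial with a planned sample size of 50" and says of a problem with 5% prevalence that "it will be identified with 92% confidence in a pilot study including 50 participants". The chance of at least one case is 1 − (1 − 0.05)^50 = 1 − 0.95^50 = 0.923, so the stated 92% reproduces. The formula assumes that every case is seen.

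**4. Sensitivity to incomplete capture.** Let m be the share of affected participants whose event goes unrecorded. The document gives no value for m, so the values below are assumptions. The chance becomes 1 − (1 − 0.05(1 − m))^50:

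| m (assumed) | Recorded prevalence | Chance of at least one recorded case |
|---|---|---|
| 0 | 5.0% | 0.923 |
| 10% | 4.5% | 0.900 |
| 20% | 4.0% | 0.870 |
| 50% | 2.5% | 0.718 |

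**5. Illustration of selective loss (all inputs assumed).** Suppose 10 of 50 stop attending before Day 7 with a 20% overdose risk, and 40 attend with a 5% risk. Expected events are 10 × 0.20 + 40 × 0.05 = 2 + 2 = 4, or 4/50 = 8%. If the EMR and other routes recover none, one or both of the two events among non-attenders, the recorded rate is 2/50 = 4%, 3/50 = 6% or 4/50 = 8%. The result runs from halved to unaffected, depending on a recovery share that the document does not give.

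**The case against.** The strongest reply is that the two rows are not the only route of capture. The EMR needs no attendance, and collection from it stops only on formal withdrawal, which is not the same as missing visits. Both items return at 1 month. Adverse events are to be tracked continuously. Participants come daily for dispensing, with honoraria, and anyone who reports sleeping more than usual or shows other signs of excess opioid effect is referred at once. The examples of toxicity listed for SROM (sedation, respiratory depression, bradycardia) are all covered by the daily POSS and vital signs. A Day 7 mark can be a look-back over the whole week and does not bar earlier recording. The Day 3 peak is stated for methadone only. Overdose, hospitalisation and death are also listed as secondary outcomes.

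Most of this stands, and it rules out three stronger readings:

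- *Events in people who stop attending are missed and the rate is biased downward.* This does not follow. They can be missed, but the EMR, the 1-month items and adverse event tracking may recover them. The 8% against 4% contrast needs zero recovery, which the document does not imply.
- *Dosing decisions wait for Day 7.* They do not, since visible toxicity is assessed every day. Only a resolved off-site event could escape.
- *The article lacks a missed-visit procedure or a rule for unknown Day 7 status.* The full protocol or analysis plan may contain these, so their absence here is no finding.

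What the reply leaves open is narrower. The secondary list places overdose at 1, 3, 6 and 12 months, so the Day 7 row is the scheduled item for the primary window. The EMR is cited for events during follow-up, and the article uses OAT follow-up phase for the period after the first 7 days, so first-week coverage is unclear. A community reversal may never reach a clinic record. Tracking events as they occur depends on someone asking, and the schedule shows no specific question until Day 7.

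**Conclusion.** The concern holds as a point about a stated schedule. Table 2 places the only specific first-week questions on overdose and hospitalisation/death at Day 7, although the visits at which to ask them already take place daily and the primary outcome and hold rule need the answers sooner. A resolved off-site overdose on Day 3 may wait up to 4 days for a scheduled question, if it does not emerge through the 24-hour report, clinical contact, the EMR or adverse event tracking. It can be lost if the participant also stops attending and the event never reaches the EMR.

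The size of the loss cannot be derived from the document. The stated 92% is correct as calculated and falls only to the extent that events go unrecorded: 0.900 at an assumed 10% and 0.870 at an assumed 20%. A reader might infer that the primary result is invalid or certainly understated; the other capture routes mean that the document does not support that. This is a cheap improvement, not a must-fix error.

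**What to change.** - In Table 2, mark both rows on each of Days 2 to 7, worded as since the last visit.
- In Secondary outcomes, state that the EMR source for overdose, hospitalisation and death also covers Days 1 to 7, including for participants who miss the Day 7 visit without withdrawing from the study.

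This brings Table 2 into line with the primary outcome window and with the commitment in Monitoring to track events continuously. It changes only when data are collected and implies no dosing or management rule. The cost is a table edit, one sentence and about one minute per existing visit, with no new visit or procedure. Recruitment is ongoing, so the change would help only participants enrolled after it; for those already enrolled, the EMR clarification still applies.
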